**5.7 Limitations**

None.

**5.8 Potential sources of bias**

The main factors that could affect insulin sensitivity, and consequently, insulin secretion are physical activity and weight change. Physical activity will be evaluated with questionnaires at the beginning and at the end of the study. This factor will be taken into account in the analyses. However, some data suggest that calcium supplementation could induce weight loss [65, 66]. If significant weight loss is observed between the treatment and placebo group, it will be difficult to discriminate the beneficial effects of calcium and vitamin D on insulin sensitivity and secretion from those induced by weight loss. However, this will be adjusted for in multivariate analysis.

Seasonal variation can influence endogenous 25OHD production. With small number block randomisation, this effect will be minimised by distributing patients equally between treatment groups within a small time frame.

1. Dunstan, D.W., et al., *The rising prevalence of diabetes and impaired glucose tolerance: the Australian Diabetes, Obesity and Lifestyle Study.* Diabetes Care, 2002. **25**(5): p. 829-34.
2. Cameron, A.J., et al., *Overweight and obesity in Australia: the 1999-2000 Australian Diabetes, Obesity and Lifestyle Study (AusDiab).* Med J Aust, 2003. **178**(9): p. 427-32.
3. Giulietti, A., et al., *Monocytes from type 2 diabetic patients have a pro-inflammatory profile. 1,25-Dihydroxyvitamin D(3) works as anti-inflammatory.* Diabetes Res Clin Pract, 2007. **77**(1): p. 47-57.
4. Targher, G., et al., *Serum 25-hydroxyvitamin D3 concentrations and carotid artery intima-media thickness among type 2 diabetic patients.* Clin Endocrinol (Oxf), 2006. **65**(5): p. 593-7.
5. Cigolini, M., et al., *Serum 25-hydroxyvitamin D3 concentrations and prevalence of cardiovascular disease among type 2 diabetic patients.* Diabetes Care, 2006. **29**(3): p. 722-4.
6. Li, Y.C., et al., *1,25-Dihydroxyvitamin D(3) is a negative endocrine regulator of the renin-angiotensin system.* J Clin Invest, 2002. **110**(2): p. 229-38.
7. Billaudel, B., L. Barakat, and A. Faure-Dussert, *Vitamin D3 deficiency and alterations of glucose metabolism in rat endocrine pancreas.* Diabetes Metab, 1998. **24**(4): p. 344-50.
8. Tanaka, Y., et al., *Effect of vitamin D3 on the pancreatic secretion of insulin and somatostatin.* Acta Endocrinol (Copenh), 1984. **105**(4): p. 528-33.

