**5.6 Statistical analyses**

Analyses will be performed using SPSS version 15.0. Skewed data will be log-transformed or examined using non-parametric tests. Differences in delta HOMA-IR between the treatment and the placebo group will be compared by two-sample unpaired *t* test. The change in DI and in ISR (assessed by deconvolution analysis of C-peptide levels and the insulinogenic index) and also the total area under the curve of C-peptide by deconvolution analysis will be compared between groups with unpaired *t* test. Analyses will be performed to assess changes in inflammatory markers, intact osteocalcin, adiponectin, blood pressure, lipid profile, FFA and weight with a two-sample unpaired *t* test. A *P*-value of ≤0.05 will be considered statistically significant. The endpoints will be adjusted for risk factors of type 2 diabetes: age, sex, BMI, family history of type 2 diabetes and physical activity. The following covariates will also be adjusted for: sunlight exposure and VD and calcium intake. Finally, the variables that predict response to treatment will be identified with multiple linear regression analyses. We will perform data analysis on an intention-to-treat principle. We will also perform analysis on patients who achieved >75% compliance with study medication as well as those on active treatment who achieved target 25OHD levels ≥75 nmol/L.

*Sample size calculation*

Sample size calculation is based on the difference in delta HOMA-IR [0.15 ± 0.18 (SD)] observed in a similar population of overweight subjects with pre-diabetes before and after a mean weight loss of 9.8 kg [64]. This change in HOMA-IR resulted in improved beta-cell function and reduction in the area under glucose curve during OGTT. This change in HOMA-IR was therefore considered clinically significant and was chosen for sample size calculation. A sample of 32 participants in each group will have 90% power to detect a difference in delta HOMA-IR of 0.15 with a standard deviation of 0.18 and 2-sided alpha of 0.05. Assuming a drop out rate of 20%, we will study a total of 80 participants.

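### The weight-change adjustment and the compliance and 25OHD-achiever analyses condition on post-randomisation events and need to be kept apart from the intention-to-treat result

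*Protocol*

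**What the plan says.** The primary hypothesis (Protocol 3.1) is that combined vitamin D and calcium improves insulin sensitivity, secretion and beta-cell function compared with placebo. Section 5.6 tests the change in HOMA-IR with an unpaired t test and adopts the intention-to-treat principle.

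Three further statements matter here.

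- **Weight.** Section 5.8 notes that "some data suggest that calcium supplementation could induce weight loss". It says that a significant weight difference between arms would make the supplement's own effect hard to separate from that of weight loss. It then offers the remedy: "However, this will be adjusted for in multivariate analysis". Body weight is also one of the secondary outcomes in 3.2.
- **Covariates.** Section 5.6 adjusts the endpoints for age, sex, BMI, family history, physical activity, sunlight exposure and vitamin D and calcium intake, and names no time point. Under 5.5, weight and the three questionnaires are collected at baseline and at the end. Section 5.8 repeats this for one of them: "Physical activity will be evaluated with questionnaires at the beginning and at the end of the study", and says that the factor will enter the analyses.
- **Subsets.** Section 5.6 adds an analysis of patients with more than 75% compliance, "as well as those on active treatment who achieved target 25OHD levels ≥75 nmol/L". No placebo counterpart and no comparator is given for the second group.

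Section 5.7 lists no limitations.

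**The concern.** The primary hypothesis asks what assignment to the combined treatment does to insulin outcomes by whatever route, weight included. By the protocol's own account weight loss may be one of those routes. Adjusting for it estimates something else: the part of the effect that does not pass through weight. Even that part is identified only if nothing unmeasured drives both weight change and HOMA-IR change, and diet and activity during the trial are obvious candidates. The adjustment is also triggered by the data, because 5.8 frames it for the case where a significant weight difference is seen. It is presented as a cure for bias and not as a separate mediation question. End-of-study activity, sunlight or intake, if used as covariates, would raise the same difficulty.

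For the achievers, the protocol itself supplies reasons why attained 25OHD may be prognostic. Section 1.2 links the winter low in vitamin D to worse glycaemic control. Section 5.2 cites data that requirements may be higher in obesity, although its dosing source found no influence of weight or fat mass. Section 5.8 relies on small blocks to balance season between arms, and selecting one arm on attained 25OHD undoes that balance. The compliance subset is at least defined in both arms, but adherence is still behaviour after randomisation.

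At stake is which number is presented as the treatment effect. Section 3.1 defines adequate supplementation by the 75 nmol/L threshold, and section 2 calls failure to ascertain adequacy the main weakness of earlier trials. The achiever result could therefore easily be given more weight than it can bear.

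**Working it through.** **The plan's own figure.** Inputs from 5.6: difference 0.15, SD 0.18, two-sided alpha 0.05, power 90%.

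- Normal formula: n = 2 × (1.960 + 1.282)² × (0.18/0.15)² = 30.3, so 31 per arm.
- The t-based calculation gives 31.25, so 32 per arm, which matches "A sample of 32 participants in each group will have 90% power".
- Power of the t test at 32 per arm is 90.7%.
- Allowing for 20% drop-out: 64/0.8 = 80.

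The stated sample size reproduces. It belongs to the unadjusted comparison.

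**Weight adjustment.** Section 5.6 takes the 0.15 from a before-and-after change that came with a mean loss of 9.8 kg. Treating that as a linear, causal slope (an assumption) gives 0.15/9.8 = 0.0153 HOMA-IR units per kg. The protocol gives no expected weight difference between arms, so the kilograms below are assumed. The total effect is set at 0.15. Power is for a t test with 32 per arm and the SD held at 0.18, although adjustment could also change the SD.

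| Weight difference | Part removed | Share of 0.15 | Effect left | Power |
|---|---|---|---|---|
| 0 kg | 0 | 0% | 0.150 | 90.7% |
| 1 kg | 0.015 | 10% | 0.135 | 83.8% |
| 2 kg | 0.031 | 20% | 0.119 | 74.3% |
| 3 kg | 0.046 | 31% | 0.104 | 62.4% |

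**Achievers.** The protocol states no comparator, so this step assumes a comparison with all placebo patients. It also assumes no true treatment effect, 32 per arm, SD 0.18, and a correlation ρ between attained 25OHD (as a continuous variable) and HOMA-IR improvement. If a proportion p of the active arm reaches target and z is the standard normal cut-point exceeded with probability p, the spurious benefit is

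ρ × 0.18 × φ(z)/p,

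where φ(z)/p is 0.798 at p = 0.5, 0.497 at p = 0.7 and 0.195 at p = 0.9. For example, at p = 0.5 and ρ = 0.2: 0.2 × 0.18 × 0.798 = 0.029. Type I error was simulated with 8,000 runs per setting, giving a Monte Carlo standard error near 5% of √(0.05 × 0.95/8000) = 0.24 percentage points.

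| Attainment | Spurious benefit, ρ = 0.2 to 0.4 | Share of 0.15 | Type I error, ρ = 0.2 / 0.3 / 0.4 |
|---|---|---|---|
| 50% | 0.029 to 0.057 | 19 to 38% | 8.0 / 11.5 / 18.2% |
| 70% | 0.018 to 0.036 | 12 to 24% | 6.3 / 8.5 / 10.4% |
| 90% | 0.007 to 0.014 | 5 to 9% | 5.4 / 5.3 / 6.1% |

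A normal approximation with standard error √(1/(32p) + 1/32) in SD units gives 6.5 to 11% at 70%, in line with the simulation. At ρ = 0 there is no bias and the simulated error is 4.8 to 5.4%. The protocol states neither attainment nor ρ.

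**The case against.** The best defence is that the main comparison is sound. It is an unadjusted t test under intention to treat, the sample size rests on it, and 5.6 introduces the subset analyses as additions. That stands. A reader might infer that the primary result itself is biased, and the text does not support this. Nothing says that the adjusted or subset results replace the t test, although 5.6 does not rank the adjusted results below it either.

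Secondly, 5.8 openly describes a wish to separate direct effects from those of weight loss, which is a legitimate mediation question. That also stands in part: the model may be kept. But 5.8 offers it as a correction for bias and only if a difference appears, so more than a label is missing.

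Thirdly, covariate timing is often left to a statistical analysis plan, which is not at hand. A reader might infer that end-of-study values will be used. Section 5.6 does not say so. It leaves this open, and 5.8 makes it a real possibility for physical activity.

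Fourthly, a reader might infer that achievers will be tested against the whole placebo arm. Section 5.6 names no comparator, and a within-arm or descriptive summary fits the wording as well. Neither a comparison with all placebo patients nor one with the achievers' own baseline would be randomised, but the type I error figures apply only to the former.

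Finally, attainment may be high. Section 5.2 provides for a dose increase at 8 weeks, and in the 4000 IU study it cites no subject remained below 75 nmol/L, although those were healthy adults. At 90% attainment the inflation is small.

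**Conclusion.** The concern holds for the supplementary analyses and for how results are labelled, not for the primary test. Followed as written, the weight adjustment in 5.8 does not estimate the total effect in the primary hypothesis. The two subsets in 5.6 are not randomised comparisons, and the time point of several covariates is left open.

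The sizes are illustrations. The loss of 10 to 31% of the target effect depends on an assumed 1 to 3 kg difference and on reading a before-and-after change as a linear causal slope. Type I error of about 8 to 18% at 50% attainment, 6 to 11% at 70% and 5 to 6% at 90% depends on an assumed comparison with all placebo patients and an assumed correlation of 0.2 to 0.4. The protocol cannot settle any of these, so it would go too far to say that either analysis will mislead by a known amount.

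**What to change.** In 5.6, state that the intention-to-treat total effect is the reported result and that any covariates are values measured before randomisation.

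In 5.8, replace the conditional adjustment with a weight-change-adjusted model that is reported whether or not weight differs, labelled as an exploratory mediation analysis and given with its assumptions.

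Label the analysis of patients with more than 75% compliance as exploratory. Present the 25OHD achievers descriptively, without a P value.

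A complier-average estimate that uses randomisation as an instrument for reaching 75 nmol/L would not be a sound substitute. Active patients below target still receive calcium and some vitamin D. Sections 1.3 and 2 credit calcium with effects of its own on insulin secretion and sensitivity, and 1.2 cites a plateau for HbA1c at 65 nmol/L, below the target. Assignment could therefore act without attainment, and the exclusion restriction fails on the protocol's own rationale.

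The cost is wording and slightly fewer inferential claims from the supplementary analyses. The 80 participants and the 90.7% power of the unadjusted test for a total effect of 0.15 do not change. Because the weight rule is triggered by the data, the change should be made before unblinding.
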